**2. LIST OF ABBREVIATIONS**

| Term | Description                          |
|-------------|---------------------------------------------|
| AE          | Adverse Event                               |
| CA          | Competent Authorities                       |
| CRA         | Clinical Research Associate                 |
| CAUTI       | Catheter Associated Urinary Tract Infection |
| CBC         | Complete Blood Count                        |
| CRO         | Clinical Research Organization              |
| CRF         | Case Report Form                            |
| CFU         | Colony Forming Unit                         |
| EC          | Ethics Committee                            |
| EU          | European Union                              |
| FDA         | Food and Drug Administration                |
| GCP         | Good Clinical Practice                      |
| GMP         | Good Manufacturing Practice                 |
| Hb          | Hemoglobin                                  |
| IB          | Investigator's Brochure                     |
| ICH         | International Conference on Harmonization   |
| IRB         | Institutional Review Board                  |
| IP          | Investigational Product                     |
| IMP         | Investigational Medicinal Product           |
| MOH         | Ministry Of Health                          |
| NO          | Nitric Oxide                                |
| NOS         | Nitric Oxide Synthase                       |
| NZW         | New Zealand White                           |
| IDSA        | Infectious Diseases Society of America      |
| QA          | Quality Assurance                           |
| QC          | Quality Control                             |
| RNS         | Reactive Nitrogen Species                   |
| SAE         | Serious Adverse Event                       |
| SD          | Standard Deviation                          |
| SOC         | System Organ Class                          |
| SOP         | Standard Operating Procedure                |
| UTI         | Urinary tract Infection                     |

### 3. INTRODUCTION

#### 3.1 Background

According to recent publications by the World Health Organization (WHO) [1], hundreds of millions of patients are affected by health-care associated infections worldwide each year, resulting in prolonged hospital stays, long-term disabilities, deaths, and financial losses for health systems. The most common hospital-acquired infection is urinary tract infection (UTI), which accounts for almost 40% of all nosocomial infections [2]. According to the Center of Disease Control (CDC), most hospital-acquired UTIs are associated with catheterization [3]. In fact, urinary catheter-related bacteriuria is the most common health care associated infection worldwide [4]. Studies have showed that *Escherichia coli* is the most common bacterial pathogen responsible for catheter-associated UTIs (CAUTIs) [5, 6].

Planktonic bacteria can adhere to surfaces on catheters and colonize, creating a persistent environment called a biofilm [7, 8]. These colonies consist of bacteria that are highly differentiated and resistant to standard antibiotics [9], augmenting the potential of these pathogens to cause infections in patients with indwelling catheters.

In recent years, catheters coated with various antiseptic materials have been investigated for their ability to prevent biofilm formation and bacteriuria [10-13]. Several manufactures have marketed either antimicrobial-impregnated or silver-coated catheters as representing a technology to reduce CAUTI risk. More specifically, Nitric oxide (NO), an endogenously produced gas molecule, which plays an important role in host defense against various pathogens, has also been investigated for its potential to prevent biofilm formation [14, 15].

Using a novel approach, Regev-shoshani et al., generated antiseptic barrier on urinary catheters by impregnating them with NO [16]. Upon immersion in urine, these catheters demonstrated slow release of NO over a 14-day period and were able to prevent bacterial colonization and biofilm formation on their luminal and exterior surfaces [14]. In addition, they were also shown to inhibit the growth of *Escherichia coli* within the surrounding media and eradicated bacterial concentrations of up to  $10^4$  CFU/ml, suggesting the high potential of NO to prevent CAUTIs.

#### Nitric Oxide

In 1987, endothelium derived relaxing factor was identified as nitric oxide (NO), a small lipophilic free radical gas molecule, that easily cross the plasma membrane into the cytosol [17, 18]. NO which is produced endogenously by various cell types including immune cells was shown to be involved in cell

signaling, vasodilatation of smooth muscle, neurotransmission, and regulation of wound healing. In addition, NO also plays a significant role in host defense against a large variety of pathogens [18-21].

NO is naturally synthesized in mammalian cells by an NADPH dependent nitric oxide synthase enzyme (NOS) which catalyzes oxidation of L-arginine to produce citrulline and NO [22]. Three isoforms of NOS are recognized in humans: two are constitutively expressed (endothelial NOS and neuronal NOS) and produce only nanomolar concentrations of NO. The third isoform, inducible NOS (iNOS), is expressed mainly by immune cells such as macrophages and neutrophils and is responsible for the high output of micromolar concentrations of NO following a variety of stimuli. In normal subjects, iNOS is up-regulated in macrophages and other immune cells following infection and/or stimulation by cytokines [21]. iNOS-induced elevation of NO together with other superoxide ions, produced by immune cells during inflammation results in the generation of several reactive nitrogen species (RNS) which are extremely toxic to bacteria. Indeed, during the last decade several mechanism by which NO and its RNSs elicits anti-bacterial and bactericidal activity were detected [21, 23-28]. These mechanisms were shown to affect bacteria in multiple compartments ranging from the outer membrane through the cytoplasm and into the nucleolus. In addition, NO was also found to be involved in the prevention of biofilm formation and biofilm dispersal [14, 15, 29].

### **NO half-life (T1/2)**

The half-life of NO, which corresponds to the time it takes to lose half of its pharmaceutical and physiological activity, is very short [17]. In the blood, NO disappears within seconds following binding with high avidity to hemoglobin (Hb). According to hakim et al., interaction between NO and Hb occurs in a 4:1 ratio, thus NO is unlikely to reach the body circulation as a free radical and to act as a circulating humoral substance [30]. In plasma fluids, NO react with molecular oxygen to form nitrite or with superoxide to form peroxynitrite (ONOO), which further decompose to nitrite and nitrate. It is assumed that reaction of NO with oxygen in aqueous solutions at a concentration typical of those that exist in cells are relatively slow, with a half-life for NO of about one hour [31].

### **Technologies used in urinary catheters to prevent infections**

The most researched technical innovation in catheter design over the past 10 years has been the introduction of antimicrobial coatings applied to catheter surfaces or impregnated into the catheter material aimed to prevent bacterial attachment and biofilm formation [10-13]. Several manufactures have marketed

either antimicrobial-impregnated or silver-coated catheters as representing a technology to reduce CAUTI risk.

Silver has long been recognized as an antimicrobial agent with demonstrated activity against uropathogens through multiple mechanisms of action such as inactivation of vital enzymes by reacting with thiol groups, enhancing pyrimidine dimerization by photodynamic reaction, and causing cell wall changes induced by electron dense granules [13, 32]. A potentially more direct method of inhibiting CAUTI is to coat or impregnate catheters with antimicrobials active against expected uropathogens. An antimicrobial agent used for catheter impregnation is nitrofurazone, a topical nitrofurantoin, which has a spectrum of activity against many potential uropathogens, which involves interference with multiple bacterial intracellular targets including ribosomes, DNA and cell wall.

Study results have shown that silver impregnation had little effect on bacterial adherence, while nitrofurazone impregnation had a significant effect, yet only for the first 5 days following catheterization [33]. The results in the study do not support a role for silver urinary catheters to prevent CAUTIs by decreasing bacterial adherence. The results of this study and others lead to the conclusion that a solution of using a device that will be able to prevent UTIs for long time and without using antibacterial drugs has great potential for the health sector.

In a study funded by ENOX, Regev-Shoshani et al., showed that NO-impregnated catheters exhibited superior performance compared to silver-coated catheters, and similar anti-infective properties compared to antibiotic-coated catheters, suggesting that NO-impregnated catheters can act better to prevent bacteriuria than silver alloy-coated catheter and have a better antiseptic effect [16].

### **The use of NO in prevention of biofilm formation**

The use of indwelling catheters is considered a major risk for UTI. A central part of the pathogenesis of CAUTIs involves the adherence and colonization of planktonic bacteria on catheters surface, creating a persistent environment called a biofilm. The nature of biofilm structure together with the physiological attributes of biofilm organisms confers an inherent resistance to various antimicrobial agents such as antibiotics, disinfectants or germicides. The mechanisms responsible for resistance include delayed penetration of antimicrobial agents through the biofilm matrix, altered growth rate of biofilm organisms, and other physiological changes due to the biofilm mode of growth [34].

### *In Vitro Studies*

In recent years, catheters coated with various antiseptic materials have been investigated for their ability to prevent biofilm formation on catheters, and bacteriuria [10-13]. More specifically, several techniques which involve the release of NO were developed and studied for their potential to prevent biofilm formation on catheters. For example, in an *in vitro* model of a catheterized urinary bladder, Carlsson et al. showed that a combination of nitrite and ascorbic acid, which releases low concentration of NO (maximum of 10ppm), effectively killed a clinical isolate of *Escherichia coli*, and a reference strain after 24 hour exposure [15].

Using a novel approach, in a study funded by ENOX, Regev-shoshani et al. [16] generated antiseptic barrier on urinary catheters by impregnating them with NO. These NO-impregnated catheters were then immersed in urine to simulate a clinically relevant static environment. According to results, slow release of NO from NO-impregnated catheters during a 14 days period prevent bacterial colonization and biofilm formation of *Escherichia coli* on their luminal and exterior surfaces. In addition, NO was able to eradicate up to  $10^4$  CFU/ml of bacteria within the surrounding media [14]. In another study, Regev-Shoshani et al. showed that NO-impregnated and antibiotic Nitrofurazone (NF)-coated catheters were equivalent in their antimicrobial activity and eradicated all bacteria in planktonic and biofilm states [16].

The mechanism by which NO prevents biofilm formation beyond simple eradication of the biofilm forming bacteria needs to be further clarified, yet it is speculated that NO prevents the attachment of bacteria and inhibition of biofilm formation in a mechanism which involves reduction and modification of proteins that mediate cell-substrate and cell-cell interactions [35-37].

In light of the results obtained by Regev-Shoshani et al., which showed that NO-impregnated catheters exhibited superior performance compared to silver-coated catheters, and similar anti-infective properties, compared to antibiotic-coated catheters, we propose that NO-impregnated catheters can act better to prevent bacteriuria than silver alloy-coated catheter and have a better antiseptic effect. These data highlights the great potential of NO in the prevention of biofilm formation, an attribute that might ease the burden of CAUTIs on health systems. Finally, the high efficiency of NO-impregnated catheters in preventing planktonic growth and biofilm formation is consistent and supportive of the Infectious Diseases Society of America (IDSA) guidelines.

### **NO-impregnated catheters Animal safety trials**

In February, 2014, ENOX conducted safety trials for the NO-impregnated catheters were in NZW rabbits. The experimental design included two equally-

sized groups (n=5, each group): one group was subjected to urethral catheterization with NO-impregnated indwelling urinary catheter, while the control group was subjected to urethral catheterization with non-impregnated indwelling urinary catheter. Safety-related parameters were evaluated following an exposure period of 7 successive days to the indwelling urinary catheter.

**Study results:**

- Mortality events did not occur in both experimental groups prior to the scheduled termination time point
- No treatment-related adverse reactions were observed among all experimental animals following the urethral catheterization and throughout the entire 7-day observation period
- No marked differences were observed in the mean group body weight values between both experimental groups, determined prior to the urethral catheterization and at the end of the 7-day observation period
- There were no statistically significant differences in mean group hematology and biochemistry values, body weights and rectal temperatures among the test device-treated group vs. the respective values determined in the control device animals
- Local urethra mucosal irritation was found similarly in both groups

According to electron microscopy images, obtained at the end of the 7-day catheterization period, it seems that sections from NO-impregnated catheters exhibited reduced biofilm formation on the exterior and luminal surfaces, compared to control group. Although the concentration of the biofilm-forming bacteria was not examined in this study, it is likely that NO-impregnated catheters may have a beneficial effect on the ability of bacteria to form biofilm on catheter surface.

**3.2 Study Hypothesis**

NO-impregnated Foley catheters indwelled for  $7-21 \pm 7$  days are safe and tolerable.

### 3.3 Summary

This study proposes to use NO-impregnated catheters takes into consideration previous knowledge of:

- (a) The known infection prevention properties of NO-impregnated catheters (ENOX innovation method).
- (b) Nitric oxide activity as vasodilator.
- (c) NO's very short half-life within the blood system, which minimize the time of active NO presence in the blood and its potential hazard to distal organs.
- (d) NO-impregnated catheters have a safe profile in a rabbit model.
- (e) Long term use of NO in a gas formation which has been approved by FDA to treat premature infants through mechanical respiratory rout.

NO-impregnated catheter method was developed by ENOX to prevent nosocomial infection. Bacterial colonization rates in catheterized patients are high. Moreover, bacterial density and biofilm formation in the catheter is high and consistent for days/weeks (but tend to increase over time). NO-impregnated catheters reduces bacterial density and can prevent biofilm formation [16], and were found to be safe in animal trials.

## 4. STUDY OBJECTIVES

### 4.1 Primary Objective

#### **Safety and Tolerability:**

- Assess the safety of NO-impregnated Foley catheters indwelling for 7-21±7 days in patients undergoing radical prostatectomy
- Assess the tolerability of NO-impregnated Foley catheters indwelling for 7-21±7 days in patients undergoing radical prostatectomy

### 4.2 Observational

- Proportion of patients (%) who prematurely discontinued the study for any reason
- Measure and compare the biofilm formation on the surface of NO-impregnated versus non-impregnated Foley catheters after indwelling for 7-21±7 days
- Measure bacteriuria (by urine culture) for NO-impregnated versus non-impregnated Foley catheters prior to insertion, on catheter insertion day, every day during hospitalization, on catheter removal day, and 30-45 days after catheterization
- Compare occurrences of clinically significant UTIs following catheterization with NO-impregnated and non-impregnated Foley catheters
- Record different species of bacterial contaminations

## 5. STUDY END POINTS

### 5.1 Primary End Point(s)

#### **Safety:**

- Determine AEs and SAEs associated with NO-impregnated catheters
- Proportion of patients (%) who prematurely discontinued the study due to AEs or SAEs

#### **Tolerability:**

- Proportion of patients (%) who prematurely discontinued the study due to AEs or SAEs associated with NO-impregnated catheter

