#### 7.5.1 Criteria for Treatment Discontinuation

- AEs that are suspected to be related to NO-impregnated catheters, according to physician discretion

- Blood pressure and heart rate above or below the 20% of the normal ranges for the patient baseline

A patient whose treatment was discontinued for any reason should complete all study assessment including the follow up visits.

Concomitant medication (i.e. antibiotics) given during the study will not be a reason for treatment early discontinuation.

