### **The causality of the AE will be assessed as:**

**Unrelated:** when the AE is clearly and incontrovertibly due to extraneous causes (disease, environment, etc.).

**Unlikely related:** if the AE meets at least two of the following criteria: 1) it does not follow a reasonable temporal sequence from catheterization; 2) it could readily have been produced by the patient's clinical state, environmental or toxic factors, or other modes of therapy administered to the patient; 3) it does not follow a known pattern of response NO.

**Possibly related:** if the AE meets at least two of the following criteria: 1) it follows a reasonable temporal sequence from catheterization; 2) a causal relationship to the experimental treatment cannot necessarily be reasonably excluded and an alternative explanation (e.g., concomitant drug or concomitant disease) cannot be reasonably suggested as causing the SAE; 3) it follows a known pattern of response to NO.

**Probably related:** if the AE meets at least three of the following criteria: 1) it follows a reasonable temporal sequence from catheterization; 2) it cannot be reasonably explained by the known characteristics of the patient's clinical state, environmental or toxic factors, or other modes of therapy administered to the patient; 3) it disappears or decreases on catheter removal, and it follows a known pattern of response to NO.

The date of onset, a description of the AE, severity, seriousness, action taken, relationship to the NO-impregnated catheter, outcome of the event, and date of resolution will be recorded. It should be documented if considered an SAE.

An SAE is defined as an AE that

- Results in death
- Is life-threatening
- Requires re-hospitalization or prolongs existing inpatient hospitalization
- Results in persistent or significant disability or incapacity
- Is an significant medical event which requires medical intervention to prevent any of the above outcomes

**Significant medical events** are those that may not be immediately life-threatening, but may jeopardize the patient and may require intervention to prevent one of the other serious outcomes listed above. Occurrences resulting in an AE will normally be considered serious by this criterion.

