**The following information should be provided to accurately and completely record the event:**

- 1) Investigator name
- 2) Patient number
- 3) Patient initials
- 4) Patient demographics
- 5) Clinical event
  - Description of the event
  - Date of onset
  - Severity of the event
  - Treatment
  - Relationship to study catheter (causality)
  - Actions taken regarding study catheter
- 6) If the AE results in Death
  - Cause of death (whether or not the death is related to study catheter)
  - Autopsy findings (if available)
- 7) Medical history CRF (copy)
- 8) Concomitant medication case report (copy of relevant CRF page )
- 9) Any relevant reports (laboratory, discharge, x-Ray, etc.)

This information should be sent to the sponsor.

The procedures for notification of suspected serious unexpected adverse reactions (SUSARs) shall be carried out in accordance with the Israeli MOH. SAEs should be reported by the ENOX BIOPHARMA to EC/IRB according to local requirements.

Patients who have had an SAE during the treatment period must be followed clinically until all parameters (including laboratory) have either returned to normal or have stabilized or are otherwise explained.

Any newly emergent SAEs, after treatment is discontinued or the patient has completed the study and is considered to be related to the investigational medicinal product (IMP) or study participation, should be recorded and reported immediately. The post-study period for the purpose of SAE reporting is routinely up to 30 days following last study visit or until SAE is resolved or stabilized.

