#### **Safety and Tolerability:**

The study objective is to demonstrate a safety and tolerability profile.

Adverse events will be coded according to coding dictionaries (MedDRA version 16.1 or higher) and presented in tables by System Organ Class (SOC) and Preferred Term (PT). Additional tables will be generated for adverse events associated with NO-impregnated catheters.

95% CI will be calculated for the proportion of patients who prematurely discontinued the study for any reason and due to any AE or SAE.

Chi-square test or Fisher's Exact test (as is appropriate) will be used for analyzing the difference in proportions between the study groups. Laboratory results will be summarized in appropriate tables by time. Changes from baseline will be calculated and presented as well.

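### Two of the three primary endpoints and the main adverse-event causality record refer only to the NO-impregnated catheter, so the six controls supply no background for them

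*Protocol*

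**What the plan says.** Section 5.1 of the Protocol lists three primary endpoints, and the synopsis repeats them:

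- Safety, first item: "Determine AEs and SAEs associated with NO-impregnated catheters".
- Safety, second item: "Proportion of patients (%) who prematurely discontinued the study due to AEs or SAEs", with no reference to either catheter type.
- Tolerability: "Proportion of patients (%) who prematurely discontinued the study due to AEs or SAEs associated with NO-impregnated catheter".

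Section 6.1 assigns six patients to NO-impregnated catheters, followed by six controls with non-impregnated ones, open label.

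Relatedness is described in several ways. In section 12, after the causality categories, the item kept for each adverse event is "relationship to the NO-impregnated catheter, outcome of the event, and date of resolution will be recorded". The list of contents for a serious-event report, also in section 12, asks for "Relationship to study catheter (causality", which fits either arm. Section 13.4 tabulates the maximal relationship to the tested catheters by treatment group. Section 11.2 refers to study medication.

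On analysis, section 13 (Safety and Tolerability) gives confidence intervals for discontinuation for any reason and for any AE or SAE. It then says that a chi-square or Fisher test "will be used for analyzing the difference in proportions between the study groups". Events associated with the NO-impregnated catheter get additional tables. Section 13.4 (Tolerability Assessments) analyses all non-completion, non-completion due to AEs, and time to withdrawal.

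One of the two treatment-discontinuation criteria in section 7.5.1 is "AEs that are suspected to be related to NO-impregnated catheters, according to physician discretion".

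**The concern.** Take two patients with the same record: urethral irritation from the catheter, followed by leaving the study because of it. In the NO arm the event can count for both NO-limited primary endpoints. In the control arm it cannot count for either, because that patient never had an NO-impregnated catheter.

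The background matters here. In the rabbit study described in section 3.1, local urethral irritation appeared similarly with impregnated and non-impregnated catheters. Local irritation is also a listed potential NO-related event (section 11.4.2 and Appendix 5). Under section 12 an event is possibly related if it meets two of three criteria. Timing after catheterization and a known pattern of response to NO are enough, so ordinary catheter irritation in an NO patient can qualify.

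The controls are the only source in this trial for separating the two effects. If relatedness is never judged for them, no later analysis plan can reliably recover it.

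**Working it through.** **Which patients can score on each primary endpoint**

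| Endpoint (section 5.1) | NO arm (6) | Control arm (6) |
|---|---|---|
| NO-associated AEs/SAEs | can score | cannot score |
| Study discontinuation due to any AE/SAE | can score | can score |
| Study discontinuation due to NO-associated AEs/SAEs | can score | cannot score |

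Two of three endpoints have no control counterpart.

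**What relatedness is judged against**

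| Place | Reference | Usable for controls? |
|---|---|---|
| Section 12, adverse-event record | NO-impregnated catheter | no |
| Section 12, serious-event report | study catheter | yes |
| Section 13.4, AE tables by group | tested catheters | yes |
| Section 7.5.1, first criterion | NO-impregnated catheters | no |

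If the first row governs the case report form, the section 13.4 table has no valid control entry for non-serious events. If the second and third rows govern, the section 12 record is wrongly worded. Both cannot hold.

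**Endpoint against analysis.** Section 5.1 defines tolerability by discontinuation due to NO-associated events. Section 13.4 analyses all non-completion and non-completion due to any AE. Neither is the stated endpoint.

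**Size.** The protocol gives no event rate, effect size or power. Its N of 12 is a judgement, so there is no plan figure to reproduce. The opening rule of section 13 summarises categorical variables by study group with 95% intervals. Applied to the tolerability endpoint, the control row is 0/6. The exact upper limit is 1 − 0.025^(1/6) = 0.459, so the interval is 0 to 45.9%. If the zero is structural, that interval describes nothing.

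The following is an illustration only. Suppose both catheters cause a related event in the same proportion p of patients, with p assumed.

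- *Chance that the NO arm shows the higher count, control fixed at zero:* 1 − (1 − p)^6. At p = 0.1 this is 1 − 0.9^6 = 0.47; at p = 0.3 it is 1 − 0.7^6 = 0.88. If relatedness were judged in both arms, exact enumeration over 6 versus 6 gives 0.29 and 0.38.
- *Two-sided Fisher p against 0/6:* 3/6 gives 0.182, 4/6 gives 0.061, 5/6 gives 0.015. At least 5 of 6 are needed for significance at 5%.
- *Chance of reaching 5 of 6:* 6p^5(1 − p) + p^6, which is 0.0001 at p = 0.1, 0.011 at p = 0.3 and 0.109 at p = 0.5. Judged in both arms, Fisher rejects with probability at most 0.006.

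The effect is therefore on how the table reads. False significance stays rare unless event rates are high.

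**The case against.** The hypothesis (section 3.2) and the primary objective (section 4.1) concern only the NO-impregnated catheter, and comparison between arms appears only among the observational endpoints. On that view the NO-limited endpoints are descriptive for one arm and simply do not apply to controls. Section 12 counts any untoward event as an AE whether related or not, and section 13.4 tabulates all AEs by group, so an all-cause comparison is already planned. The study has 12 patients and disclaims power. Over-attribution would run against the device, which is the cautious direction in first-in-human use.

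Much of this stands, and it rules out three stronger readings that a reader might infer:

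- **That the plan tests NO-associated proportions against a built-in zero.** No passage expressly does so. The test sentence in section 13 directly follows any-reason and any-AE/SAE discontinuation, where controls can score. Section 13.4, including its Cox model, is not limited to NO-associated withdrawal. Only a broad reading of the generic reference to proportions would bring the endpoint in.
- **That every primary endpoint is one-sided.** The second safety endpoint takes any AE or SAE.
- **That the stopping rules as a whole are one-sided.** The blood pressure and heart rate criterion in section 7.5.1, withdrawal for an SAE (7.5.2) and study stop for death (7.5.3) apply to both arms. Patients who stop treatment still complete follow-up, so 7.5.1 does not directly create a study discontinuation.

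What the objection does not remove is the contradiction over what causality is recorded against, or the mismatch between the tolerability endpoint and its analysis. All-cause tables do not supply a relatedness judgement for controls that was never made.

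**Conclusion.** The point holds in a limited form. The primary tolerability endpoint and the first primary safety endpoint cannot be met by half the patients. The adverse-event causality record in section 12 conflicts with the serious-event report and with the tables in section 13.4, and the tolerability endpoint differs from its planned analysis. Followed as written, the primary tolerability result cannot separate an NO effect from an ordinary Foley effect.

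This conclusion rests on the wording alone. The percentages above depend on assumed event rates and, for the Fisher figures, on a test that the protocol does not clearly apply to these endpoints. They should not be cited as the trial's error rate. With 6 per arm and no claim to power, the defect is one of definition and interpretability. It should be settled before data are collected.

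**What to change.** - In sections 5.1, 12 and 13, and in the matching synopsis entries, define relatedness once as *related to the assigned study catheter (NO-impregnated or non-impregnated)*. Bring the study-medication wording in section 11.2 into line.
- Record relatedness on that definition prospectively for all 12 patients.
- State the tolerability endpoint as discontinuation due to AEs or SAEs related to the assigned catheter, report it by arm, and make section 13.4 (Tolerability Assessments) analyse that quantity. All non-completion and all-AE non-completion can stay as further summaries.
- Limit any between-arm comparison to that definition or to all-cause events and discontinuations. Present NO-associated events as a descriptive listing for the NO arm.
- The first criterion in section 7.5.1 uses the same one-sided wording. The sponsor should reconcile it with sections 12 and 13.4. What the clinical rule should be is for the sponsor and the investigator.

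The cost is wording, plus a matching causality item on the case report form, which is not among the documents and so could not be checked. No extra patients, visits or tests are needed.
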